# The effect of luseogliflozin on bone microarchitecture in older patients with type 2 diabetes: study protocol for a randomized controlled pilot trial using second-generation, high-resolution, peripheral quantitative computed tomography (HR-pQCT)

**DOI:** 10.1186/s13063-020-04276-4

**Published:** 2020-05-05

**Keywords:** Type 2 diabetes, Luseogliflozin, SGLT2 inhibitor, HR-pQCT, Fracture, Bone, Randomized controlled trial, Pilot

## Abstract

**Background:**

Older patients with type 2 diabetes mellitus (T2DM) have an increased risk of bone fracture independent of their bone mineral density (BMD), which is explained mainly by the deteriorated bone quality in T2DM compared to that in non-diabetic adults. Sodium-glucose co-transporter (SGLT) 2 inhibitors have been studied in several trials in T2DM, and the Canagliflozin Cardiovascular Assessment Study showed an increased fracture risk related to treatment with the SGLT2 inhibitor canagliflozin, although no evidence of increased fracture risk with treatment with other SGLT2 inhibitors has been reported. The mechanism of the difference in the fracture risk between the SGLT2 inhibitors is unknown, but the differences among the SGLT2 inhibitors in the selectivity of SGLT2 against SGLT1 may affect bone metabolism, since among the SGLT2 inhibitors the selectivity of canagliflozin is lowest. We will investigate whether the SGLT2 inhibitor luseogliflozin, which has the higher SGLT2 selectivity, affects bone metabolism by using high-resolution, peripheral quantitative computed tomography (HR-pQCT) which provides direct in vivo morphometric information about the bone microarchitecture.

**Methods/design:**

This is a single-center, randomized, open-label, active-controlled, parallel pilot trial. Eligible participants are older (age ≥ 60 years) individuals with T2DM with HbA1c levels at 7.0–8.9%. A total of 24 participants will be allocated to either the luseogliflozin group (taking luseogliflozin) or the control group (taking metformin) in a 1:1 ratio to compare the groups’ changes in bone microarchitecture of the radius and tibia which are analyzed by HR-pQCT before and at 48 weeks after the administration of each medication. The laboratory data associated with glycemic control and bone metabolism will be collected every 12 weeks during the study. Recruitment began in June 2019.

**Discussion:**

The reason that we use metformin as an active control is to avoid yielding differences in glycemic control between the luseogliflozin and control groups. Besides, metformin is considered to have a neutral effect on bone. This trial should reveal the effect of luseogliflozin on bone metabolism in older patients with T2DM.

**Trial registration:**

The study was registered with the University Hospital Medical Information Network (UMIN000036202) on 1 April 2019 and with the Japan Registry of Clinicla Trials (jRCTs071180061) on 14 March 2019.

## Background

Type 2 diabetes mellitus (T2DM) is well known as a cause of secondary osteoporosis. Individuals with T2DM have shown a 40–70% increase in the risk of hip fracture compared to age- and gender-matched healthy adults [1, 2]. However, the bone mineral density (BMD) of the spine and femur in individuals with T2DM has been reported to be comparable to, or somewhat higher, than that in non-diabetic adults [1, 3]. The cause of the elevated fracture risk in the individuals with T2DM is, thus, suspected to be deteriorated bone quality due to (1) the accumulation of advanced-glycation end-products in the bone collagen fibers and (2) decreased bone turnover as a result of exposure to hyperglycemia [3, 4].

High-resolution, peripheral quantitative computed tomography (HR-pQCT), first developed in 2004, is a three-dimensional imaging technology. HR-pQCT is effective for determining bone quality based on an evaluation of microarchitecture, volumetric BMD, and geometry separately for the cortical and trabecular compartments of the distal radius and tibia. This technique can often detect a fracture risk that is independent of the BMD determined by dual-energy x-ray absorptiometry (DXA) [5–7]. Several studies evaluated the bone microstructure in individuals with T2DM using first-generation HR-pQCT, and the results regarding the deteriorated bone quality were controversial [8–11]. A second-generation HR-pQCT scanner was recently developed with an improved ability to analyze bone microarchitecture; this second-generation HR-pQCT scanner has not yet been used in a study of individuals with T2DM.

Sodium glucose co-transporter 2 (SGLT2) inhibitors have garnered attention as a breakthrough drug for patients with T2DM, as it was revealed that SGLT2 inhibitors have the potential to improve cardiovascular outcomes in T2DM [12–14]. However, there are several concerns about the SGLT2 inhibitors’ effects on bone metabolism regarding the following: (1) stimulation of parathyroid hormone (PTH) and fibroblast growth factor 23 by the increased serum phosphate levels via tubular reabsorption in phosphate, (2) weight loss, and (3) volumetric depletion and fall risk (e.g., orthostatic hypotension and postural dizziness) [15].

The U.S. Food and Drug Administration recently strengthened the warning for the SGLT2 inhibitor canagliflozin related to an increased risk of bone fracture, based on the outcomes in the Canagliflozin Cardiovascular Assessment Study (CANVAS) [16]. In that study, the rate of fracture adverse events (AEs) in the canagliflozin group was significantly increased compared to that of the placebo group (4.0% vs. 2.6%, respectively) [17]. It was also reported that canagliflozin treatment was associated with a small but significant reduction in the BMD of the total hip and with increases in bone biomarkers of formation (osteocalcin) and resorption (collagen type 1 β-carboxytelopeptide) compared to placebo controls [18], which might be explained, at least in part, by canagliflozin-treated patients’ weight loss. In contrast, no evidence of an increased fracture risk has been reported in other cardiovascular outcome trials evaluating the effects of SGLT2 inhibitors in the patients with T2DM [12, 19, 20].

There is no clear explanation for the difference in fracture risk between the CANVAS trial and other trials. It is possible that among the SGLT2 inhibitors, the selectivity of SGLT2 against SGLT1 may affect bone metabolism and the fracture risk, since the selectivity of canagliflozin is the lowest among the SGLT2 inhibitors under clinical development [21]. However, it is not yet known whether the CANVAS trial’s finding of an increased rate of fracture events related to canagliflozin treatment would be reproduced by treatment with other SGLT2 inhibitors, especially those with higher SGLT2 selectivity.

## Methods/design

### Objective

This study will aim to determine whether treatment with the SGLT2 inhibitor luseogliflozin (which has high SGLT2 selectivity) affects bone metabolism by assessing the changes in bone microstructure using second-generation HR-pQCT in older patients with T2DM.

### Study design

This is a pilot trial to assess the effect of SGLT2 inhibitors on bone metabolism. We designed a single-center, randomized, open-label, parallel-group, active-controlled trial for patients with T2DM whose conditions have never been complicated by osteoporosis. We will randomly assigned 24 patients using a 1:1 ratio to the luseogliflozin group (receiving additional treatment with luseogliflozin) or the control group (receiving additional treatment with metformin). The study follow-up duration is 48 weeks. The study will be conducted at Nagasaki University Hospital, Japan. The study design is summarized in Fig. 1.

**Fig. 1 Fig1:**
[figure not shown]
The study design. The eligibility check is conducted and the patient’s informed consent is obtained at visit 1. Only the patients who satisfy the run-in criteria at visit 2 are enrolled in the study; they are randomized at a 1:1 ratio to the luseogliflozin group (administered luseogliflozin 2.5 mg) and the control group (administered metformin 500 mg). The bone microarchitecture of the patients is analyzed before (visit 2) and 48 weeks after the administration of each medication (visit 6). *BMD* bone mineral density, *SD* standard deviation, *T2DM* type 2 diabetes mellitus

### Outcomes

The primary outcome measures are changes in the predicted bone strength as determined by second-generation HR-pQCT, evaluated using the parameters of: (1) bone stiffness and (2) the estimated failure load of the radius and tibia of the nondominant body side. For each parameter, any change will be determined based on the difference between the measurement results at baseline (week 0) and week 48.

The study’s secondary outcome measures are as follows: (1) the changes in the structures of cortical bone, trabecular bone, and the bone morphology measured by HR-pQCT as described below in the “Image measurements” section from baseline (week 0) to week 48; (2) the changes in the laboratory data values, including the levels of glycated hemoglobin (HbA1c) from week 0 to weeks 12, 24, 36, and 48; (3) the changes in the areal BMD of the lumbar spine (L1–L4), femoral neck, and distal radius estimated by DXA from week 0 to week 48; (4) the incidence of vertebral fracture or femoral fracture from week 0 to week 48; and (5) changes in the bone metabolic markers from week 0 to week 48.

In addition to the primary and secondary outcomes, we will evaluate adverse effects from both luseogliflozin and metformin (control agent). We will also evaluate the recruitment rate and consent rate.

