### Statistical analyses

As stated above in the “Objectives” section, the primary outcome of this study is the extent of luseogliflozin’s effects on bone-quality change. Hence, the primary data analysis will be conducted using the set of participants with sufficient exposure to the allocated drugs. For this reason, we will use a per-protocol set (PPS), the definition of which includes the adherence ratio, as the target population in the primary data analysis. The same analyses will be conducted on a full analysis set (FAS) modified FAS (mFAS) to provide supplemental information about the influence of selecting PPS subjects on the results.

As the primary and the secondary data analyses, the adjusted mean and the 95% confidence intervals (95%CIs) of the bone-deterioration effect of the treatment group will be estimated as regression coefficient and its standard error, for the respective primary and secondary outcome measures, under a linear regression model with the following two covariates: the baseline measurement of the respective measures and the stratification factor in the randomization (i.e., sex). This study is set up as a pilot study, but we will test the null hypotheses that “the mean of the bone-quality deterioration effect of the treatment group is 0” by determining whether the 95%CIs contain the null hypotheses.

The respective analysis sets are defined as follows. The intention-to-treat (ITT) population is defined as all participants registered for this trial; the safety analysis set (SAS) population is defined as the participants in the ITT population with at least one administration of luseogliflozin/metformin. The full analysis set (FAS) population is defined as the participants in the SAS for whom data about the predicted bone strength after the administration of luseogliflozin/metformin at one or more scheduled visits are available. The PPS is defined as the participants in the FAS with the primary outcome measure. Other criteria for the PPS will be determined before the database lock of this study. We defined the modified FAS (mFAS), the definition of which is a relaxed version of PPS by allowing missingness of the data of predicted bone strength at week 48 only if the data of the items at withdrawal from this study are obtained.

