As a safety analysis, tabular summaries of AE incidence among subjects in a SAS will be created. All hypothesis testing will be conducted at the significance level of 0.05 (two-sided). The data collected will be summarized using the arithmetic mean, the standard deviation, and the quantiles. All statistical analyses are conducted under the computing environment R (R Foundation for Statistical Computing, Vienna, Austria).

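### Four primary measures are each tested at two-sided 0.05 with no lead measure, order, adjustment or success rule; if any one counts as a finding, the false-positive chance is about 8 to 18.5%

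*Protocol article*

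**What the plan says.** The Outcomes section of the protocol article uses the plural: "The primary outcome measures are changes in the predicted bone strength", "evaluated using the parameters of: (1) bone stiffness and (2) the estimated failure load of the radius and tibia of the nondominant body side". It continues: "For each parameter, any change will be determined based on the difference between the measurement results at baseline (week 0) and week 48". Each parameter at each site therefore gives one week 0 to week 48 contrast between the groups, and there are four of them.

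The Statistical analyses section estimates the treatment effect separately, "for the respective primary and secondary outcome measures, under a linear regression model with the following two covariates", namely "the baseline measurement of the respective measures and the stratification factor in the randomization" (sex). On inference it says: "This study is set up as a pilot study, but we will test the null hypotheses", and this is done "by determining whether the 95%CIs contain the null hypotheses". The closing paragraph of that section sets the level: "All hypothesis testing will be conducted at the significance level of 0.05 (two-sided".

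Nowhere does the article single out one parameter or site, order the four tests, split the alpha, require several measures to agree, or say that the intervals are descriptive. The same model and the same 0.05 rule apply to the secondary measures.

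**The concern.** With four separate tests and no rule for combining them, the stated 0.05 describes each test but not the primary question as a whole. A reader cannot tell beforehand which result would show that luseogliflozin affects bone strength: stiffness or failure load, radius or tibia, one of them or all of them. That choice would be made after the results are known, and a single significant result out of four could be presented as the primary finding. The secondary HR-pQCT measures add many more tests under the same rule.

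**Working it through.** **Inputs from the article**
- Primary measures: 2 parameters × 2 sites = 4 (Outcomes).
- Level: 0.05 two-sided for every test; decision by an unadjusted 95% interval (Statistical analyses).
- Sample: 24 patients, 12 per group (Study design, Sample size estimation).
- Model: intercept, treatment, baseline value and sex, so residual df = 24 − 4 = 20 if all 24 are analysed.

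**Inputs assumed**
- The correlations among the four measures are not given, so a range is shown. *Within site* is stiffness against failure load in the same bone; *between sites* is radius against tibia.
- Any one significant measure is read as a primary finding. The article states no such rule.

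**Step 1. The plan's own figure.** For one test the error is 1 − 0.95 = 0.05. Simulating the planned regression under the null with all four measures identical, which amounts to one test, gave 0.0504 (100,000 runs). So 0.05 is right per test.

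**Step 2. Four tests, limiting cases**
- Independent: 1 − 0.95⁴ = 0.185. The upper bound under any correlation is 4 × 0.05 = 0.20.
- Stiffness and failure load acting as one test within each site, sites independent: 1 − 0.95² = 0.0975.
- All four identical: 0.05.

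**Step 3. Four correlated tests.** Chance of at least one rejection when there is no effect, from simulated four-variate normal test statistics:

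| Within site | Between sites | At least one false positive |
|---|---|---|
| 0.95 | 0 | 12.5% |
| 0.95 | 0.3 | 12.2% |
| 0.95 | 0.5 | 11.6% |
| 0.95 | 0.7 | 10.6% |
| 0.98 | 0.7 | 9.8% |
| 0.95 | 0.9 | 8.8% |
| 0.98 | 0.9 | 8.3% |
| 0.99 | 0.9 | 7.9% |

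Simulating the planned regression itself (df 20) gave similar values: 12.1% at 0.95/0.5, 11.0% at 0.95/0.7 and 8.1% at 0.99/0.9. Weaker correlation moves the figure up: 14.4% at 0.8/0.5 and 17.0% at 0.5/0.3.

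**Step 4. Secondary HR-pQCT measures.** The Image measurements section lists 4 trabecular, 3 cortical and 4 morphology parameters, which is 11, and 3 volumetric densities as a separate group. The secondary outcome list names cortical structure, trabecular structure and morphology but not density.
- Read literally: 11 × 2 sites = 22 tests; 22 × 0.05 = 1.1 expected false positives if there is no effect.
- With the densities: 14 × 2 = 28 tests; 28 × 0.05 = 1.4.

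Expected counts do not depend on the correlations.

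**Step 5. Effect of possible repairs**
- One lead measure, or a fixed sequence, at 0.05: 5.0%.
- Bonferroni at 0.05/4 = 0.0125: 1 − 0.9875⁴ = 4.9% if independent; 2.2 to 4.6% in the simulated regression cases with correlated, non-identical measures.
- Power cost of 0.0125, which is also Holm's first step: for an assumed true difference of 1 residual SD with 12 per group, the noncentrality is 1/√(2/12) = 2.449. With df 20 the critical t rises from 2.086 to 2.744, and power falls from about 64% to about 41%.

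**The case against.** **No success rule is stated, so no inflated error rate follows.** This stands in part. If all four measures had to be significant, the error would be at most 5%. The article does not adopt that rule either, so the defect is the missing rule, and the 8 to 18.5% is what follows under the any-one reading.

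**A reader might infer that the plan claims 5% overall and is wrong.** The article does not support that. It gives 0.05 as the level of its hypothesis tests and never claims a family-wise rate. Nor does it suggest an intention to report selectively: all four measures are prespecified, estimates are promised for each, and outcome assessors are blinded.

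**The top of the range is unrealistic.** Two strength measures of the same bone are unlikely to be independent, so 18.5% is a limiting case. With strong within-site correlation, about 8 to 12.5% is the more plausible part of the range, but this is a judgement that the documents cannot settle.

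**It is a pilot.** The Sample size estimation section rests on feasibility and precision and makes no power claim, and the Discussion lists small size and short follow-up as limitations. This lowers the severity. It does not remove the point, because the Statistical analyses section commits to testing despite pilot status.

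**Multiplicity belongs in the analysis plan.** A detailed procedure usually does. Here, however, the article is not silent: it fixes the level for all testing and the unadjusted 95% interval as the decision rule. An adjustment placed in a separate plan would depart from that text.

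**Correction costs power where possible harm is being studied.** This stands. The loss from about 64% to 41% in the example is a good reason to prefer a lead measure or estimation over Holm or Bonferroni. It is also ordinary practice to leave secondary outcomes unadjusted, provided that they carry no significance claim.

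**Conclusion.** The point holds as a missing decision rule. Four primary measures are each tested at two-sided 0.05, and nothing says which one leads or how many must succeed. If any one significant result is taken as a primary finding, the chance of at least one false positive is about 8 to 9% at an assumed between-site correlation of 0.9. It is about 10 to 12.5% at assumed within-site 0.95 to 0.98 and between-site 0 to 0.7, and 18.5% under independence. It reaches 5% only if the four measures behave as one. These figures rest on the any-one reading and on correlations that the documents do not give. The secondary HR-pQCT tests add about 1.1 to 1.4 expected false positives if there is no effect. In a 24-patient pilot this should be corrected, but it does not undermine the design.

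**What to change.** Before any week-48 data are analysed, amend the Outcomes and Statistical analyses text in one of two ways.

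1. **Lead measure with a fixed sequence.** Name one parameter at one site as the lead primary measure, list the other three in order, and test each at two-sided 0.05 only if all those before it are significant. The primary family is then held at 5% without a stricter threshold for the lead measure.
2. **Estimation only.** Replace the hypothesis-test sentence with a statement that the 95% intervals for all four primary measures are for estimation and that no significance claim will be made. This fits the precision rationale in the Sample size estimation section. The sentence fixing 0.05 for all testing must then be brought into line.

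In either case, state that the secondary intervals are descriptive. Holm over the four measures would also control the error but is the weaker option here because of its power cost.

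The cost is a protocol wording change, with the registry entries updated if they describe the primary outcome in the same way; no extra patients, visits or scans are needed. Under option 1, later measures carry a significance claim only if the earlier ones succeed. Under option 2, no formal claim is made at all.

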### Withdrawal criteria

Participants will be withdrawn from this trial after randomization if they meet any of the following criteria: (1) are exhibiting an increase in HbA1c level that is ≥ 0.5% of the baseline (week 0) for any two successive visits; (2) have a HbA1c level > 10.0% at any visit; (3) the occurrence of any AE that is ≥ grade 3 of the Common Terminology Criteria for Adverse Events (CTCAE) ver. 4.0; (4) are showing any fracture(s) with the exception of an occult fracture; (5) have requested withdrawal from the study; (6) have requested a change in, or the discontinuation of, the diabetes treatment; (7) it is determined that it is inappropriate for the patient to continue in the study by the investigators because of the progression of an underlying disease or a complication, or the occurrence of an unidentified disease; and (8) it is judged by the investigators that it is inappropriate for the patient to continue participating in the study for any other reason.

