## Discussion

The main purpose of this study is to determine whether treatment with the SGLT2 inhibitor luseogliflozin affects bone metabolism in older patients with T2DM by using second-generation HR-pQCT.

For the evaluation of this effect of luseogliflozin, we use metformin as an active control drug for the following three reasons: (1) we should avoid yielding differences in glycemic control between the luseogliflozin and control groups. If we use a placebo control, the effect of luseogliflozin on bone may be confounded by the improvement of glycemic control and (2) metformin is reported to have a neutral effect or at least a not-negative effect on bone [24, 25]. We can avoid overestimating the efficacy of luseogliflozin for bone metabolism by using metformin as a control drug; (3) metformin is the most commonly used antidiabetic agent worldwide and is recommended by most of the relevant guidelines as a first-line therapy for T2DM [14, 26, 27].

Participants treated with an α-GI and/or a DPP-4 inhibitor in addition to metformin can also be enrolled in the study. There is no report demonstrating an increased risk of fracture associated with α-GIs and DPP-4 inhibitors [25, 28]. In addition, those drugs are used widely in Japan for older patients with T2DM.

It is recognized that bone strength is determined by bone mass, morphology, and microstructure. In a clinical setting, an individual’s bone mass is generally represented as the BMD assessed by DXA [7]. We will identify the precise changes in bone strength brought about by 1-year treatment with luseogliflozin by using second-generation HR-pQCT, which can detect the changes of bone morphology and microstructure. Sundh et al. reported that increased cortical porosity determined by HR-pQCT is associated with hip fracture in postmenopausal women, independent of areal BMD in the femoral neck determined by DXA even after adjusting for other fracture risk factors [29]. Samelson et al. reported that the trabecular and cortical bone structure evaluated by HR-pQCT can predict a future risk of femoral fracture, which is independent of the estimated fracture risk provided by the fracture-risk assessment tool (FRAX) [7].

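### If the arms differ in HbA1c, the per-protocol comparison understates the difference at every visit, because participants withdrawn for high or rising HbA1c are left out of it

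*Protocol article*

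**What the plan says.** The Outcomes section makes HbA1c change a secondary outcome at four visits: "the levels of glycated hemoglobin (HbA1c) from week 0 to weeks 12, 24, 36, and 48". The Statistical analyses section applies one form of analysis "for the respective primary and secondary outcome measures, under a linear regression model with the following two covariates", the covariates being the baseline value and sex. It names the PPS "as the target population in the primary data analysis" and gives the full analysis set (FAS) and mFAS a supplementary role. It names no separate set for secondary outcomes.

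The sets are defined by bone data, not HbA1c data. "The PPS is defined as the participants in the FAS with the primary outcome measure", and the Outcomes section defines that measure as a change from week 0 to week 48. The mFAS relaxes this: week-48 bone strength may be missing if data at withdrawal exist.

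Two withdrawal criteria depend on HbA1c. Participants are withdrawn if they "are exhibiting an increase in HbA1c level that is ≥ 0.5% of the baseline (week 0) for any two successive visits", or if they "have a HbA1c level > 10.0% at any visit". Table 1 schedules laboratory data at weeks 0, 12, 24, 36 and 48 and at withdrawal.

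The Discussion gives as the first reason for the metformin control that "we should avoid yielding differences in glycemic control between the luseogliflozin and control groups". The abstract gives the same reason.

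**The concern.** Under these rules the outcome being analysed helps to decide who is analysed. A participant whose HbA1c climbs is withdrawn, has no week-48 scan, and so drops out of the PPS. All their HbA1c values go with them, including those from visits attended before withdrawal. If one arm controls glucose less well, it loses more of its poor responders, and the remaining participants look more alike than the randomised arms were.

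This matters because the comparator was chosen so that a bone difference would not be a glycaemia difference. HbA1c by arm is the natural evidence on whether that succeeded. The protocol does not guarantee equality, since the two arms follow different escalation paths in the Interventions section. A selected HbA1c comparison is weakest in exactly the case where it is needed, namely when glycaemia does differ.

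**Working it through.** **The protocol's own figures.** It gives no HbA1c withdrawal rate, SD, expected change or equality margin. Its only related figure is the sample size, 2 × 12 = 24, which follows from the cited pilot-study rule and says nothing about this point.

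**Who is in each comparison.** Consider a participant withdrawn for HbA1c before week 48.
- PPS: absent at all four visits, because there is no week-48 bone change.
- FAS: read literally, also absent. It needs post-dose bone strength at a scheduled visit, and apart from the withdrawal examination week 48 is the only post-baseline scan in Table 1.
- mFAS: present up to withdrawal if the withdrawal data exist, and absent afterwards. The rise criterion needs two successive visits, so it cannot act before week 24.
- A participant who first meets the rise criterion at weeks 36 and 48 is already at the week-48 scan visit and is not lost.

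**Size at each visit.** Simulation with 400,000 participants per arm, so sampling error is negligible. From the protocol: entry HbA1c from 7.0% to below 9.0%, the four visits and both withdrawal rules. Assumed: rise rule in percentage points; baseline uniform from 7.0 to 8.95; SD of change 0.6, 0.8 or 1.0; within-person correlation 0.6; mean change in the better arm −0.5 or −0.2; no titration effect over time; every withdrawn participant has the withdrawal scan. For a true arm difference of 0.50 points:

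| SD | Better-arm mean | PPS wk 12 / 24 / 36 / 48 | mFAS wk 12 / 24 / 36 / 48 | HbA1c withdrawals per 12, better / worse arm |
|---|---|---|---|---|
| 0.6 | −0.5 | 0.41 / 0.39 / 0.41 / 0.42 | 0.50 / 0.50 / 0.44 / 0.42 | 0.27 / 1.67 |
| 0.6 | −0.2 | 0.35 / 0.31 / 0.35 / 0.37 | 0.50 / 0.49 / 0.39 / 0.37 | 0.89 / 3.56 |
| 0.8 | −0.5 | 0.37 / 0.34 / 0.37 / 0.38 | 0.50 / 0.48 / 0.41 / 0.38 | 0.77 / 2.42 |
| 0.8 | −0.2 | 0.32 / 0.28 / 0.32 / 0.34 | 0.50 / 0.48 / 0.36 / 0.34 | 1.60 / 4.05 |
| 1.0 | −0.5 | 0.34 / 0.30 / 0.33 / 0.36 | 0.50 / 0.47 / 0.38 / 0.36 | 1.33 / 3.01 |
| 1.0 | −0.2 | 0.30 / 0.26 / 0.30 / 0.32 | 0.50 / 0.46 / 0.35 / 0.32 | 2.24 / 4.41 |

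Shrinkage = (true − shown) / true.
- PPS, week 48: (0.50 − 0.42)/0.50 = 16% to (0.50 − 0.32)/0.50 = 36%.
- PPS, week 24 (the worst visit): up to (0.50 − 0.26)/0.50 = 48%.
- mFAS, week 24: 0% to (0.50 − 0.46)/0.50 = 8%.
- mFAS, week 36: (0.50 − 0.44)/0.50 = 12% to (0.50 − 0.35)/0.50 = 30%.
- mFAS, week 48: the same as the PPS.
- For a true 0.30, the PPS shows 0.20 to 0.26 at week 48.
- For a true difference of 0, the bias is 0 in every setting.

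**Sensitivity to the mean change.** A second model used baseline mean 7.8% and SD 0.45, between-participant SD of change 0.5 to 0.7, within-participant SD 0.2, and true differences of 0.30, 0.40 and 0.60. Week-48 shrinkage among completers was:
- better-arm mean −0.3: 25% to 41%
- −0.5: 16% to 34%
- −0.7: 9% to 26%
- −1.0: 3% to 16%

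**Does the remedy work?** In the second model, a likelihood estimate using the earlier visits returned 0.30, 0.40 and 0.60 for those true values. In the first model, carrying the withdrawal value forward gave 0.31 to 0.34 for a true 0.30 and 0.53 to 0.56 for a true 0.50. That removes the attenuation but slightly overstates the difference.

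**The case against.** A reader might infer that the HbA1c values which triggered withdrawal are collected and never used. The documents do not support that: the same analyses are planned in the mFAS, where these values count up to withdrawal. The mFAS is also meant to show how selecting the PPS affects results. What remains is that it is only supplementary, and that its weeks 36 and 48 share the problem.

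A reader might also infer that the trial plans to demonstrate equal glycaemia and would do so falsely. The protocol states no equality test, margin or intended claim. HbA1c is one laboratory value among the secondary outcomes, and the Discussion passage is a design rationale. The link to comparable glycaemia is an inference, though a natural one.

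Three further points have force.
- The PPS is named for the primary data analysis, so its use for secondary outcomes is the natural reading but not an explicit one. Modelling detail may sit in an analysis plan that is not shown. The objection here, however, is to the stated set definition combined with the stated withdrawal rules, not to missing detail.
- Titration in both arms may narrow HbA1c differences and keep withdrawals few.
- Precision is poor in any case. With 12 per arm and the second model's SDs, the SE of the difference is √(0.5² + 0.2²) × √(2/12) = 0.22 to √(0.7² + 0.2²) × √(2/12) = 0.30. The largest biases, such as 41% of 0.60 = 0.25 at the larger SD, stay below one SE.

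The last point limits the practical weight. It does not justify keeping a bias of known direction that the data already scheduled can remove.

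**Conclusion.** The point holds in a limited form. On the natural reading, the PPS comparison of HbA1c omits participants withdrawn for high or rising HbA1c at all four visits. The mFAS omits them only after withdrawal. If the arms truly differ, the PPS at every visit and the mFAS at weeks 36 and 48 understate the difference. At week 48 the understatement is roughly 3% to 41%, and in the harshest setting tried the PPS at week 24 lost 48%. If the arms are equal, there is no bias.

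The direction was the same in every setting where the arms differed. The size rests on assumed SDs, correlations, mean changes and an absence of titration effects, none of which the protocol supplies. The PPS result can describe completers, but it should not be the basis for a statement that glycaemia was comparable between the randomised arms.

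**What to change.** Add one paragraph to Statistical analyses.
- Analyse HbA1c in all treated participants, that is, the existing safety analysis set, using every observed value including the withdrawal visit.
- Fit one likelihood-based repeated-measures model for change at weeks 12, 24, 36 and 48, with arm by visit, baseline HbA1c and sex, and a simple covariance structure stated in advance.
- Report the adjusted arm difference with its 95% CI at each visit, and the number of HbA1c-triggered withdrawals by arm.
- Keep the PPS result as supplementary, and rest any statement on comparable glycaemia on the all-treated model.

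This removes the selection caused by the two HbA1c criteria, because under them withdrawal depends on HbA1c values that have been observed. Withdrawals for other reasons still need the usual missing-at-random assumption.

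No new visits or samples are needed, since laboratory data at withdrawal are already in Table 1. The downside is that a covariance structure must be chosen with 24 participants, which is why it should be simple and fixed beforehand.
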